#### Obstacle course

As described by Kunz [3], each child ran from a marking cone to a transversally positioned bench (distance: 1 m), climbed over it, turned around, crawled under the bench, ran back to the marking cone, rounded it, and passed the course two more times. Time was taken in seconds. The bench was constructed according to the German DIN 7909 standard - except for the stabilizing bar, which was left out. For transporting reasons the bench was shortened to 2 m. With a test-retest coefficient of r = 0.97 between two attempts (n = 20) within one week the obstacle course has been found to be a reliable test [3].

#### Balancing on one foot

The child was balancing on a bar of 4.5 cm width and 6.0 cm height with one foot. The choice of leg was up to the child. He or she was asked to hold the balance for 60 seconds. The free leg had to be kept in the air without touching the ground or the bar. Otherwise, time was stopped and the child was asked to move back to the correct testing position. Then, the testing time continued. During the test, an examiner counted each ground contact with the free leg as a penalty point. Total points were summed and used as score. At 30 points the test was discontinued. The test-retest correlation between two attempts within three weeks in a pilot study (n = 152) was r = 0.60 (personal communication by [name], [name], [name], [name], [name]).

#### Jumping to and fro sidewise

The child was positioned on a slip-proof board (size: 60 cm × 96 cm) with a small bar (60.0 × 2.0 × 2.0 cm) of wood separating the board into two halfs according to original test instructions published for the Karlsruher Motor Screening (KMS) by Bös and colleagues [23]. The child was asked to jump sidewise over the bar with both feet as often as possible for 15 seconds. After a rest of approximately 1 minute (individual time of recovery) the task was repeated. Jump attempts with non-simultaneous foot contacts were defined as "failed". The sum of valid jumps over the two 15-second-periods was taken. The test-retest reliability coefficient for an 8-day interval between tests lies between 0.80 and 0.90 [23].

#### Standing long jump

The child was positioned with both feet behind a line according to the KMS-test instructions [23]. The child was asked to jump as far as possible, taking off with both feet. Bending the knees and swinging the arms was allowed. The jumped distance was measured with a fixed tape on the floor and the zero point at the starting line. The child had two attempts. If the child fell backwards on its hands during or after landing, this jump was taken as an executed but failed attempt. The best valid distance of the two attempts was taken. The test-retest reliability coefficient for the standing long jump is greater than 0.80 [23,24].

#### Anthropometry and body composition

Height and weight of the children were measured to the nearest 0.1 cm and 0.1 kg in light clothing and without shoes. Skin fold thickness was determined by Holtain calliper (HSK-BI, British Indicators, UK). While the children remained standing, measurements were obtained on the right side of the body at two sites on the arm - over the triceps (midpoint of the acromion and olecranon processes on the posterior aspect of the arm) and over the biceps (midpoint of the muscle belly) - and two points on the trunk - subscapular (inferior angle of the scapula) and supra-iliac (oblique fold on the iliac crest in the mid-axillary line). The median of three measurements on each location was taken and the sum of four skin folds as well as the triceps skin fold thickness were used for analysis.

#### Blood pressure and pulse

After five minutes of rest and before starting with any of the exercise tasks, the children's blood pressure and pulse rate was measured on the right arm in triplicate with an oscillometric system (Dinamap 8100, Critikon) while sitting. Although blood pressure values measured with such a system are not concordant with results of an auscultatory system, there are good reasons for using oscillometric systems in children [25]. With very few exceptions the same investigator took these measurements. The mean of the first two readings was taken to represent the children's systolic and diastolic blood pressure. If the difference between the first and the second reading was >5 mm Hg, a third reading was used in addition to the first two measurements to calculate the mean [26].

#### Balancing backwards

According to the manual of the MOT 4-6, a motor test battery for preschool children [27], the child was asked to balance backwards on a carpet strip that was 10 cm wide and 2 m long without stepping off the strip. The way the child approached the task was optional (sliding the feet, making small or large steps). This task was repeated once. One examiner positioned behind the child judged the success (no steps apart) or failure (steps in part or completely off the carpet strip). Two successful attempts were noted as 2 points, one successful attempt was recorded as 1 point and 0 points were noted for no successful attempt.

#### Target throw

Corresponding to the instructions of the MOT 4-6 [27], the child tried to hit a round target 40 cm in diameter, fixed on the wall in 3 m distance and at the height of 1.70 m (upper border), with a conventional tennis ball. Each child had four attempts including one practice attempt. The examiner standing behind the child decided about successful hits of the target - defined as fully or partly touching the disk - and documented the results (no hit: 0 points; 1 hit: 1 point; 2 and more hits: 2 points).

#### Stand and reach

As described by Bös and colleagues [23], the child stood on a wooden box of 30 cm height, 40 cm width and 31 cm depth behind a wooden board. The child was asked to bend over without flexing the knees and to reach down as far as possible with the fingers. When the child had problems to stretch the knees, a second examiner gave support. The distance between the fingertips and the platform level was measured in centimetres. If the finger tips remained above the platform the distance was recorded in negative numbers, if they reached below platform as positive number. The test-retest reliability coefficient has been reported to range between 0.80 and 0.90 [23].

#### Static balance on a force platform

A ground-reaction force platform (*Balance-X-Sensor*^®^, *Soehnle Professional GmbH, Murrhardt, Germany*) was used for assessment of static postural balance. The device is based on three piezoelectric weighing cells located in a triangle with a sensitivity of ±1 N and a maximum load of 4 kN per cell. This platform is transferring muscle forces acting against gravity as total force and in x-y coordinates. The detection of forces within the spanning triangle is ±1N. The centre of gravity is located with an accuracy of ±1 cm at 20N. Mechanical waves produced by forces against gravity on the platform are recorded as function of time f(t) at a sampling rate of 100 Hz. The testing allows an analysis of the power spectral density distribution (PSDD) in Watt per Hertz, the average mechanical power afforded during the test as an integral of PSDD, the trace length of centre of mass displacement (mm) and the force vector area of the displacements (cm^2^). Details of the technical system are described elsewhere [28].

After calibrating the system for the specific weight of the subject, the child was placed barefoot on the platform with one foot in front of the other, balancing on a marked line with open eyes. The heel of the fore foot touched the toes of the rear foot. Arms had to be kept close to the body. The child was asked to keep this position with as little movements as possible. Test time was set at 10 seconds. After a test-stand on the platform, each child had three attempts. The best valid attempt was taken for analysis.

#### Migrant status and socio-economic status

The children's parents were asked to fill in questionnaires during each testing period (see Additional file 2 for content). Since there were families with a Russian or Turkish background and poor German skills, questionnaires were translated into these languages to ensure a valid data acquisition from the respective parents.

The assessment of migrant status was conducted according to the standard of the Kinder- und Jugendgesundheitssurvey (KiGGS), a nation wide representative survey assessing the health status of German children. Thus, a child is considered as migrant if: 1) The child has immigrated from another country and one parent was not born in Germany, or 2) both parents have immigrated to Germany or do not have the German citizenship [29].

To describe the socio-economic status (SES) the Winkler index was used [30]. For dividing experimental subjects into those with low, middle or high SES, this index uses three characteristics of each person (education, represented by the school and professional education; actual or recent professional position; net household income). In each of these three areas a score between 1 and 7 is given. Then, the sum of the three scores is calculated. Low SES is defined reaching a score ≤8, middle SES between 9 and 14 scores and high SES ≥15. If SES of both parental persons was available and the child was living with both parents, the higher score was taken to denote the SES of the child. If the child lived with either mother or father the respective parental score marked the child's SES.

#### Health related data

Parents gave information about the general health status of their child concerning the existence of chronic health problems, i.e. pulmonary, cardiac, and orthopaedic diseases. Furthermore, they answered questions about the following health-related issues: recent hospitalisations of the child, use of medication, and participation in physiotherapy or ergotherapy. This information was used only to identify children with serious chronic health problems who were excluded from the study.

Accidents and infections that were accompanied by a reduction in physical activity of the child for at least 6 hours and/or required consulting a doctor were reported by the parents' retrospectively for the previous three months (accidents) and for the previous four weeks (infections), respectively. Parents were further asked to provide information on the kind of accident and/or infection, the amount of hours with reduced physical activity due to the accident/infection of the child and, in case of reported accidents, on the kind of injury.

The average duration of the child's sleep was addressed in the questionnaire separately for weekdays and weekend.

Furthermore, the parents were asked to fill in their present height (cm) and weight (kg).

#### Leisure time activities

Media use was assessed as the daily and weekly amount of television viewing, watching videos and playing computer games in minutes, reported by the parents. Furthermore, the parents gave information on the frequency of the child's television viewing per week ("every day of the week", "for 4-6 days a week", "for 1-3 days a week", "less than 1 day a week or never").

The physical activity of the child, of the mother and of the father was assessed by questions asking for sports participation in a club and the time spent in non-organised sports. The information requested included the kind of sports participation, the frequency per week or per month and the duration per workout (for example: soccer 2 × 1 hour per week, cycling 7 × 10 min per week).

The questionnaire also asked for information about the frequency the child played outdoors ("every day of the week", "for 4-6 days a week", "for 1-3 days a week" or "seldom"). Times of outdoor play of the child with and without the mother or father were separately assessed. The parents also indicated the amount of time they spent with the child during outdoor play per week. Additionally, the parents were asked to estimate the intensity of their child's activity outdoors and also their own exertion during the joint playing time separately for each parent ("sweating and getting breathless?", answers "yes" or "no").

#### Parental evaluation of the programme and monitoring of attendance for children in the intervention group

The parents of the children in the intervention group were asked twice - half-time through the intervention and at the end of the intervention - to report their satisfaction with the organisation of the project, as well as their evaluation of the physical activity homework cards and the collection of games and exercise tasks. Furthermore, the parents appraised the children's acceptance of the programme and the effects of the intervention they might have noticed in their child. Changes in the child's characteristics specifically addressed by questions including activity level, motor skills, accident frequency, concentration, temper, and general health were documented by the parents. For each of these characteristics, a classification on a 6-point Likert-scale was requested, with additional space for comments.

The kindergarten teachers were asked to keep an attendance record to document the participation of the children in the intervention lessons.

### Data analysis

A composite motor skills score will be calculated by averaging the z-transformed results of the obstacle course, the standing long jump, the balancing on one foot task, and the jumping to and fro sidewise task to describe the baseline situation. Likewise, the changes in performance from baseline of the above motor skills tests will be z-transformed and averaged for each of the three follow-up time points. For these computations, the values of the obstacle course and the balancing task will be multiplied by "-1" to account for the fact that a low score in these tasks indicates a better performance.

Baseline data will be explored by descriptive statistics. Differences between the intervention and the control group at baseline will be analysed by two sample Students t-tests for normal distributed interval scaled variables, by Wilcoxon Tests ordinal and/or not normal distributed variables and by Chi-squared statistics for nominal variables.

The primary endpoints will be analysed by a repeated measurement analysis of covariance with the changes form baseline to the two assessments during the intervention period as dependent variables and including the fixed factors intervention, gender, and urban/rural location of the kindergarten, the random factor kindergarten and the covariate age in the model. For the composite score, the mean of the z-scores of the changes in performance and the mean of the z-scores of the baseline values are used respectively. The same statistical procedure will be used for the secondary outcome variables in an exploratory manner. Predefined gender specific subgroup analyses will be performed. Several additional explorative analyses will also be performed concerning the intervention effects on selected primary and secondary outcomes in specific subgroups, such as children with different body composition, children with low motor skills performance at baseline, children with low socioeconomic status and or with a migrant status, respectively.

As effects of the intervention are anticipated to become apparent in the entire distribution of motor skills scores, no specific threshold is presumed.

There are two primary endpoints, namely the change in moderate-and-vigorous physical activity and the composite score of changes in motor skills during the intervention period. Therefore, the Bonferroni adjusted 2 sided significance levels of 0.025 are used for the analysis of primary endpoints. For all secondary endpoints, statistical significance will be considered at p < 0.05.

Effects will be analysed primarily as intention-to-treat-analyses and additionally as per-protocol analyses.

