### Sample size justification

Assuming a gender specific effect of a physical activity intervention, the statistical power had to be strong enough to allow separate analyses for girls and boys. A group difference of 0.6 standard deviations after intervention might be relevant for preventive reasons. With an usual main level of significance α = 0.025 (two primary outcomes) and β = 0.80 power, a minimum of 53 persons per group have to be available for analysis in a non-clustered design. To account for possible missing data from both follow-up visits during the intervention period due to non-participation in both tests or due to drop-out - estimated to occur in about 5% of the participating children - sample size has to be adjusted accordingly. Since accelerometry was required for one of the primary outcomes and accelerometry data are often too incomplete for valid analysis, sample size was further increased by 20%.

Because of cluster sampling (randomisation of children into intervention or control group according to the child's kindergarten) the number of subjects needed was increased by another 30% in the initial sample size calculation. In order to meet current standards of power calculation in cluster randomised trials we performed an additional calculation considering intraclass correlation. Assuming an intraclass correlation of ρ = 0.1 [18] and an average cluster size of 17 children per kindergarten, the sample size had to be increased by 160% [19].

Thus, a total of 174 girls and 174 boys were required for the intervention group and the same numbers of boys and girls for the control group.

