#### Physical activity

Free living physical activity was assessed by accelerometry (GT1 M, ActiGraph LCC, Pensacola, US) during each assessment period. The children wore the accelerometer with an elastic waistband on the hip over one week at baseline (summertime), at the follow-up test 4-6 months later (wintertime), at the second follow-up test 10-12 months after the baseline assessment (summertime), and at the third follow-up test 2-4 months thereafter (autumn). The ActiGraph (formerly CSA/MTI) is the most commonly used accelerometer in physical activity research [21] and meanwhile well evaluated for the use in preschool children [22]. The parents kept an "accelerometer diary" to report when and why their child had taken off the accelerometer. In case of technical failure, illness or lack of data, children were asked to wear an accelerometer for an additional week. Epoch time was set to 15 seconds. Night time was defined between 9.00 p.m. and 6.59 a.m. and was excluded from analysis. Periods of ten minutes or more of continuous zero counts were classified as "non worn time" and also excluded from analysis. Only data from children who wore the accelerometer for at least 7 hours per day on at least 3 valid weekdays and 1 valid weekend day were included in the analysis. Time spent in moderate-to-vigorous physical activity was calculated by using a cut off of 420 counts/15 seconds [22]. Data on time spent in moderate-and-vigorous physical activity (MVPA) was calculated as average that was related to individual wearing time per day.

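### The listed terms of the primary change-from-baseline model omit the baseline value of the outcome: no text puts baseline MVPA in the model, and for the motor composite the next sentence implies a covariate the list leaves out.

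*Protocol article*

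**What the plan says.** The Data analysis section specifies the primary model term by term. On the outcome side: "The primary endpoints will be analysed by a repeated measurement analysis of covariance with the changes form baseline to the two assessments during the intervention". On the explanatory side: "including the fixed factors intervention, gender, and urban/rural location of the kindergarten", and then "the random factor kindergarten and the covariate age in the model". Age is the only covariate named.

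The next sentence concerns the composite alone: "the mean of the z-scores of the changes in performance and the mean of the z-scores of the baseline values are used respectively". It does not say in what role the baseline mean is used. Earlier in the same section, the only purpose given for the baseline composite is descriptive: it is formed from the four tests, ending with "the jumping to and fro sidewise task to describe the baseline situation".

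There is no corresponding sentence for percent time in MVPA. The section applies the same procedure to the secondary outcomes, so whatever is decided for the primary model carries over to them.

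**The concern.** A change score subtracts the whole baseline value. When baseline and follow-up correlate below 1, the best predictor of follow-up uses only part of the baseline deviation, so an unadjusted change score over-corrects. Two things follow if baseline is left out:

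- the residual variance is larger than it need be;
- a chance difference between arms at baseline passes partly into the estimated effect.

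Allocation was of 20 against 21 kindergartens, stratified only by location, so chance imbalance in baseline activity or motor skill is a practical possibility. Both co-primary endpoints would be affected, and with them the secondary outcomes that share the model.

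**Working it through.** **1. Does the stated sample size depend on baseline adjustment?** Inputs from Sample size justification and Data analysis: difference 0.6 SD, two-sided α = 0.025, power 80%, increases of 5% and 20%, intraclass correlation 0.1, 17 children per kindergarten.

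- n per group = 2 × (2.241 + 0.842)² / 0.6² = 52.8, rounded up to 53, as stated.
- Design effect = 1 + (17 − 1) × 0.1 = 2.6.
- 53 × 1.05 × 1.20 × 2.6 = 173.6, rounded up to 174, as stated.

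The figures reproduce with no baseline term, so the sample size neither relies on adjustment nor shows that it was planned.

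**2. Precision at child level, one follow-up visit.** Let r be the baseline-to-follow-up correlation, with equal variances σ². The protocol gives no r over the follow-up interval, so every r below is an assumption. Its test-retest values (0.60 to 0.97) are for single tests over short intervals, and none is for MVPA.

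- Variance of the change = 2(1 − r)σ².
- Variance after adjusting for baseline = (1 − r²)σ².
- Ratio, adjusted to unadjusted = (1 + r)/2.
- Excess SE without baseline = √[2/(1 + r)] − 1.

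| r (assumed) | Change, 2(1 − r) | Adjusted, 1 − r² | Ratio | Excess SE without baseline |
|---|---|---|---|---|
| 0.3 | 1.40 | 0.91 | 0.65 | 24% |
| 0.5 | 1.00 | 0.75 | 0.75 | 15% |
| 0.6 | 0.80 | 0.64 | 0.80 | 12% |
| 0.7 | 0.60 | 0.51 | 0.85 | 8% |
| 0.8 | 0.40 | 0.36 | 0.90 | 5% |
| 0.9 | 0.20 | 0.19 | 0.95 | 3% |

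**3. What this means for power at 53 per group, before clustering.** The protocol says "A group difference of 0.6 standard deviations after intervention might be relevant for preventive reasons" without stating which standard deviation is meant.

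- If it is the SD of the change, power is 80% without baseline. With it, power is 94%, 91%, 89% and 87% at r = 0.3, 0.5, 0.6 and 0.7.
- If it is the SD of the follow-up value, power without and with baseline is 64% and 84% (r = 0.3), 80% and 91% (0.5), 89% and 95% (0.6), and 96% and 98% (0.7).

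**4. Chance imbalance.** As an assumption, apply the protocol's intraclass correlation of 0.1 and cluster size of 17 to the baseline values.

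- SE of the baseline difference = √[(2.6/17) × (1/20 + 1/21)] = √(0.153 × 0.0976) = 0.12 SD.
- 95% range: ±1.96 × 0.12 = about ±0.24 SD.
- With an assumed regression slope of 0.5, an unadjusted change score at the edge of that range is shifted by (1 − 0.5) × 0.24 = 0.12 SD relative to the adjusted estimate. The planning difference is 0.6 SD.

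**5. Why step 2 does not transfer directly to this design.** With the protocol's values, the variance of a kindergarten mean is proportional to 0.1 + 0.9/17 = 0.153, of which 0.1/0.153 = 65% lies between kindergartens. The gain from adjustment therefore depends largely on the baseline-to-follow-up correlation of kindergarten means, which is unknown. Step 2 shows direction and order of size, not a forecast.

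**The case against.** The strongest reply is that the sentence after the model already supplies the baseline term. The outcome is the change, so a statement that "the mean of the z-scores of the baseline values are used respectively" has no evident meaning unless baseline is a covariate. Its opening, limited to the composite, can be read as that endpoint's version of a general rule that would cover MVPA too. The article is also a condensed account, and a full analysis plan may settle the matter.

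Much of this stands. A reader might infer from the term list that the plan does not adjust for baseline at all. For the composite, the documents do not support that: the more natural reading is an intended covariate that was left out of the list. For MVPA the general-rule reading is possible, but no sentence states it. The condensed format does not remove the point, because the article does print the model's terms, and that list and the next sentence do not agree.

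Three further inferences should be resisted.

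- **Bias.** Under randomisation the change-score comparison is unbiased; what is lost is efficiency and protection against chance imbalance. Location, gender and age are already in the model.
- **Lost children.** The Physical activity section restricts analysis to children who wore the device "at least 7 hours per day on at least 3 valid weekdays and 1 valid weekend day were included in the analysis". A child without a valid baseline week drops out because the endpoint is itself a change, and a baseline covariate would not bring that child back. Nor does the protocol state a 20% loss at each wave: it gives a single 20% increase in sample size and provides for an additional wearing week.
- **A joint model with baseline as a response, as an equivalent remedy.** It is not equivalent to a covariate. It also does not fit the composite, which averages z-transformed changes and so has no follow-up level on the baseline scale.

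**Conclusion.** The point holds as a gap and inconsistency in the model specification. Baseline is absent from the listed terms, unmentioned for MVPA, and implied but undefined for the composite. Action is needed on either reading: if a baseline covariate was intended, the list is incomplete; if not, both primary analyses give up precision that was available.

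If the listed model is followed, the SE is about 24% larger at r = 0.3, falling to about 3% at r = 0.9. This assumes equal variances, one visit, child-level variation only and an r that the protocol does not give. For the composite it is an approximation, since baseline and change are averaged z-scores. The size in the clustered design cannot be fixed from the document. The validity of the randomised comparison and the stated sample sizes (53, then 174) are not in question.

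**What to change.** In the Data analysis section, name baseline percent MVPA as a covariate in the MVPA model and the baseline composite z-score as a covariate in the motor-skills model, beside age. Reword the sentence on the composite so that it says which quantity is the outcome and which the covariate. State that each secondary outcome analysed by the same procedure is adjusted for its own baseline value. Settle this before the arms are compared.

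The cost is one term per model. No new data are needed, and no child who contributes a change score is lost, because that change already requires the baseline value. The sample size calculation can stay as it is.

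### One change-from-baseline ANCOVA is set for every secondary outcome, including 0/1/2 scores and event frequencies; unless baseline is in the model this costs precision, and the effects are hard to interpret

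*Protocol article*

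**What the plan says.** The protocol article, Data analysis, specifies for the primary endpoints a "repeated measurement analysis of covariance with the changes form baseline to the two assessments during the intervention period as dependent variables". The terms are trial arm, gender and urban/rural setting as fixed factors, plus "the random factor kindergarten and the covariate age in the model". The outcome's own baseline value is not in that list. For the composite motor score only, the section adds that "the mean of the z-scores of the changes in performance and the mean of the z-scores of the baseline values are used respectively", without saying what role the baseline mean plays. The next sentence reads "The same statistical procedure will be used for the secondary outcome variables in an exploratory manner". It makes no exception by type of variable.

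The secondary outcomes so covered include:

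- Throwing skills, measured by target throw alone, scored "no hit: 0 points; 1 hit: 1 point; 2 and more hits: 2 points".
- Balancing skills, measured in part by balancing backwards, where "Two successful attempts were noted as 2 points, one successful attempt was recorded as 1 point" and no success scores 0.
- Frequency of accidents and frequency of infections, which parents recall "for the previous three months (accidents) and for the previous four weeks (infections").

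For comparing the arms at baseline, the same section does choose tests by scale: t-tests, Wilcoxon tests or chi-squared tests.

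**The concern.** The article states this rule; it is not a detail left to a fuller plan. Two things follow from it.

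**Precision.** Taking the change as the outcome, without baseline on the right-hand side, forces the coefficient of baseline to be 1. When two measurements on a child are only weakly correlated, as is plausible for short recall windows and coarse three-level scores, the subtraction mostly adds the noise of the baseline measurement.

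**Interpretation.** A change on a 0-2 score takes only the values -2 to +2, and a child who starts at 2 can only stay or fall. The mean change therefore depends on where the children started as well as on the programme. For accidents and infections, an arm difference in the change of a count is less readable than a rate ratio.

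At stake are the throwing outcome, part of the balancing outcome, and the accident and infection outcomes, all judged at p < 0.05. A real effect on them could be missed or be awkward to express.

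**Working it through.** **1. The plan's own figure.** The article gives no precision or power figure for secondary outcomes. Its sample size for the primary outcomes reproduces: 2(2.241 + 0.842)²/0.6² = 52.8, so 53 per group; then 53 × 1.05 × 1.20 × 2.6 = 173.6, so 174 per gender and arm, with 2.6 = 1 + 16 × 0.1. The present point does not touch it.

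**2. Inputs.** From the article: 21 intervention and 20 control kindergartens, about 17 children each, one baseline and two assessments during the intervention. Assumed, because the article gives none: event rates of 0.05, 0.1 and 0.3 per child per recall window; log-scale SDs of 0.2 between kindergartens and 0.6 between children; a rate ratio of 0.6; for the scores, an even split, a floor or a ceiling pattern, with a latent shift of 0.5.

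**3. Algebra, ignoring clustering.** With unit variances and correlation ρ between any two occasions, the mean of two follow-ups has variance (1+ρ)/2. Then

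- change: (1+ρ)/2 + 1 − 2ρ
- baseline-adjusted: (1+ρ)/2 − ρ²

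At ρ = 0 the ratio is 1.5/0.5 = 3.0; at ρ = 0.2 it is 1.20/0.56 = 2.1.

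**4. With clustering, counts at rate 0.3, no effect.** Stable variance is 0.09 × (e^0.40 − 1) = 0.0443, of which 0.09 × (e^0.04 − 1) = 0.0037 lies between kindergartens and 0.0406 between children. The Poisson variance is 0.3, so ρ = 0.0443/0.3443 = 0.129. Variance of a kindergarten mean:

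- change: (0.15 + 0.30)/17 = 0.0265
- adjusted: 0.871² × 0.0037 + (0.871² × 0.0406 + 0.15 + 0.129² × 0.30)/17 = 0.0137

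The ratio is 1.93. It is lower than in step 3 because the change also cancels the kindergarten effect.

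**5. Simulation.** 4000 runs per setting, tests on kindergarten means with 39 degrees of freedom, which is the balanced equivalent of the mixed model:

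| Outcome | Test size, change | Power, change | Power, baseline-adjusted | Variance ratio (no effect / effect) |
|---|---|---|---|---|
| Count, rate 0.05 | 0.047 | 0.16 | 0.42 | 2.64 / 3.25 |
| Count, rate 0.1 | 0.048 | 0.28 | 0.67 | 2.35 / 2.90 |
| Count, rate 0.3 | 0.048 | 0.65 | 0.96 | 1.93 / 2.42 |
| Score, even split | 0.050 | 0.74 | 0.86 | 1.35 / 1.38 |
| Score, floor | 0.050 | 0.65 | 0.79 | 1.46 / 1.38 |
| Score, ceiling | 0.058 | 0.51 | 0.76 | 1.44 / 1.66 |

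The simulated correlations between baseline and follow-up were 0.02 to 0.13 for counts and 0.23 to 0.29 for scores. Test size for counts stayed between 0.047 and 0.052 at rates of 0.02 to 0.1, with 17 or with 8 children per kindergarten.

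**6. Source of the loss.** A Poisson GEE with baseline as covariate (500 runs) had power 0.39, 0.63 and 0.96 at the three rates, no better than the baseline-adjusted Gaussian analysis (0.42, 0.67, 0.96). For counts, the gain therefore comes from adjusting for baseline and not from changing the link. A proportional-odds model was not simulated.

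**7. If baseline is already a covariate.** Writing A for arm, f − b = α + τA + βb is the same model as f = α + τA + (1+β)b. The estimate of τ is identical, and the precision loss is zero.

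**The case against.** The strongest reply is that the plan may already adjust for baseline. It calls the method an analysis of covariance, and the sentence on baseline z-scores can be read as change being the outcome and baseline a covariate, with the secondary outcomes following suit. On that reading the precision loss disappears (step 7). This stands as a possibility. But the sentence concerns only the composite score, gives the baseline mean no explicit role, and sits beside a list in which age is the only covariate.

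A second reply is that kindergarten means are close to normal with 20 and 21 clusters. This is right. A reader might infer from the 0/1/2 scores and counts that the p-values are invalid; the simulated test sizes do not support that.

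A third is that a ceiling belongs to the test's scoring, and that no model lets a child at 2 improve. That also stands; what an ordinal model changes is how the effect is expressed.

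Finally, the use of Wilcoxon and chi-squared tests at baseline might be read as a contradiction. It is not: those are descriptive comparisons, and they show only that scale was considered there.

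**Conclusion.** The point holds as a minor improvement. As the model terms are listed, the change-score analysis has about 1.9 to 3.3 times the variance of a baseline-adjusted one for counts, with roughly two fifths to two thirds of its power (0.16/0.42 to 0.65/0.96). For the 0/1/2 scores the variance is about 1.35 to 1.7 times as large. These figures rest on assumed rates, effects and correlations, and on baseline being absent from the model. The difficulty of interpretation remains on either reading.

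Three stronger conclusions that a reader might draw are not supported:

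- The events need not be rare or mostly zero. The article gives no rates, and infections over four weeks, with one assessment in December to February, may be common.
- The textbook factor 2(1−ρ), which gives 1.6 to 2.0 for ρ of 0.2 to 0, should not be turned into a claim of 60-100% more children. It describes a single unadjusted follow-up without clusters, which is not this design.
- The Gaussian model as such is not what costs power for the counts.

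The reach is limited. These analyses are labelled exploratory, balancing has other measures besides the 0/1/2 score, and the primary endpoints and sample size are unaffected.

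**What to change.** In Data analysis, replace the one-procedure sentence for secondary outcomes with the following:

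- The baseline value of each secondary outcome enters its model as a covariate.
- Target throw and balancing backwards are analysed by an ordinal (proportional-odds) mixed model.
- Accidents and infections are analysed by a Poisson or negative-binomial mixed model, or a logistic one for any event.
- In these ordinal and count models the follow-up value is the outcome, and the fixed terms and the random kindergarten effect stay as they are.

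The same edit should say plainly what role the baseline mean plays for the composite score.

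The cost is modest programming and no new data, since baseline values are already collected. Effects on these outcomes would be reported as odds or rate ratios and not as mean changes. If only one step is taken, baseline adjustment is the one that recovers precision.
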